# A phase III randomized clinical trial comparing laparoscopic radical hysterectomy based on open state with abdominal radical hysterectomy in patients with early-stage cervical cancer

**DOI:** 10.1186/s13063-024-08318-z

**Published:** 2024-07-11

**Keywords:** Cervical cancer, Laparoscopic surgery, Radical hysterectomy, Phase III clinical trial, Based on open state

## Abstract

**Background:**

Cervical cancer is the fourth most frequently diagnosed cancer and the fourth leading cause of cancer death in women, The standard treatment recommendation for women with early cervical cancer is radical hysterectomy with pelvic lymph node dissection, however, articles published in recent years have concluded that the treatment outcome of laparoscopic surgery for cervical cancer is inferior to that of open surgery. Thus, we choose a surgically new approach; the laparoscopic cervical cancer surgery in the open state is compared with the traditional open cervical cancer surgery, and we hope that patients can still have a good tumor outcome and survival outcome. This trial will investigate the effectiveness of laparoscopic cervical cancer surgery in the open-state treatment of early-stage cervical cancer.

**Method and design:**

This will be an open-label, 2-armed, randomized, phase-III single-center trial of comparing laparoscopic radical hysterectomy based on open state with abdominal radical hysterectomy in patients with early-stage cervical cancer. A total of 740 participants will be randomly assigned into 2 treatment arms in a 1:1 ratio. Clinical, laboratory, ultrasound, and radiology data will be collected at baseline, and then at the study assessments and procedures performed at baseline and 1 week, 6 weeks, and 3 months, and follow-up visits begin at 3 months following surgery and continue every 3 months thereafter for the first 2 years and every 6 months until year 4.5. The primary aim is the rate of disease-free survival at 4.5 years. The secondary aims include treatment-related morbidity, costs and cost-effectiveness, patterns of recurrence, quality of life, pelvic floor function, and overall survival.

**Conclusions:**

This prospective trial aims to show the equivalence of the laparoscopic cervical cancer surgery in the open state versus the transabdominal radical hysterectomy approach for patients with early-stage cervical cancer following a 2-phase protocol.

**Trial registration:**

ChiCTR2300075118. Registered on August 25, 2023.

**Supplementary Information:**

The online version contains supplementary material available at 10.1186/s13063-024-08318-z.

## Introduction

It is estimated that 570,000 women worldwide are diagnosed with cervical cancer every year [1]. Cervical cancer is the fourth most frequently diagnosed cancer and the fourth leading cause of cancer death in women [1]. In the past 20 years, the age-standardized incidence rate and mortality of cervical cancer in China have been rising. In 2020, 109,741 new cases and 59,060 deaths of cervical cancer, accounting for 18% and 17% of the world respectively [2]. The standard treatment recommendation for women with early cervical cancer is radical hysterectomy with pelvic lymph node dissection [3]. It is divided into laparoscopic cervical cancer surgery and traditional open cervical cancer surgery.

Previous evidence from retrospective and non-randomized studies shows that minimally invasive radical hysterectomy has better surgical effects than open radical hysterectomy, including less intraoperative bleeding, shorter hospital stay, lower postoperative incidence rate, and faster functional recovery [4–7].

However, articles published in recent years have concluded that the treatment outcome of laparoscopic surgery for cervical cancer is inferior to that of open surgery. The recently completed laparoscopic approach to cervical cancer (LACC) trial showed that in patients with early cervical cancer, the risk of death after a minimally invasive procedure is 6 times higher than that after radical hysterectomy through a traditional open incision (laparotomy). Minimally invasive procedure also has a high recurrence rate compared to open access, and the overall survival rate is lower [8]. A review of the minimally invasive approach to radical hysterectomy based on population-level data from the National Cancer Database confirmed that women with cervical cancer who undergo this surgery have worse outcomes than women with cervical cancer who have the procedure performed via laparotomy [9].

The results reported by LACC make the minimally invasive treatment of cervical cancer, a common gynecological tumor, seem to be history. Some studies showed that in the single-center study, MIS radical hysterectomy for cervical cancer does not bring a worse tumor prognosis; The 5-year DFS rate in the MIS group was 87%, while in the laparotomy group, it was 86.6% (*p* = 0.15) [10]; MIS treatment for cervical cancer can improved DFS.

[name] led and presided over the real-world study(RWS) of Big data for clinical diagnosis and treatment of cervical cancer in China [11]. Through the analysis of stage IA1(LVSI +)-IIA1 cervical cancer, they concluded that (1) in patients with stage IA (LVSI +)-IB1, when the tumor diameter is less than 2 cm, patients with any one of the high-risk factors or two or more medium risk factors requiring postoperative adjuvant treatment, the oncology outcome of laparoscopic surgery is no worse than that of open surgery. (2) Simple comparison of laparoscopic and open surgery for stage IB2 cervical cancer, laparoscopic surgery oncology outcomes are not inferior to open surgery, but must be standard treatment cases, that is, there is no preoperative adjuvant therapy, standard surgery, and postoperative adjuvant therapy. (3) The oncological outcome of laparoscopy for stage IIA1 Cervical cancer is no less than that of laparotomy. It should be said that the above results are encouraging. However, another RWS study based on the US national database was also published in NEJM during the same period as the LACC Trial study, “Survival after Minimally Invasive Radical Hysterectomy for Early-Stage Cervical Cancer” [9].

In addition, the results of the two studies are similar. Although the results are still controversial, the common results of RCT and RWS research have reached the highest level of evidence, so it is necessary to conduct extensive and in-depth research and explore why a minimally invasive procedure for cervical cancer is not like the results of laparotomy.

LACC researchers have suggested several possible reasons why surgical treatment of cervical cancer in minimally invasive surgery(MIS) is inferior to that in laparotomy: this includes the application of uterine manipulators, the establishment of pneumoperitoneum through carbon dioxide insufflation, the method of vaginal incision in vivo, and the experience of surgeons in MIS [8, 9, 12, 13]. During minimally invasive hysterectomy, uterine manipulators are often used for retraction and visualization, which may cause tumor cell proliferation and increase the tendency of tumor proliferation [8, 9]. The way of intracorporeal colpotomy in laparoscopy is considered to increase the possibility of tumor exposure to the abdominal cavity and tumor dissemination [12, 14, 15].

In solid tumor models, the current research results are uncertain whether CO_2_ pneumoperitoneum has an impact on immune suppression and tumor recurrence. In vitro studies have shown that cervical cancer cells stimulated in a CO_2_ pneumoperitoneum environment, after a short period of inhibition, have increased proliferation ability and decreased invasion, migration, and adhesion ability [16]. Clinical retrospective studies have shown that exposure to circulating CO_2_ in cervical cancer may lead to tumor spread to the abdominal cavity, with a higher recurrence rate [12, 16]. Therefore, we are not sure whether CO_2_ pneumoperitoneum is at high risk of recurrence and poor survival in patients undergoing minimally invasive radical hysterectomy, and we can take gasless pneumoperitoneum as a protective measure. Gasless laparoscopic surgery is a combination of traditional open surgery and current laparoscopic techniques, which uses physical and mechanical devices to lift the anterior abdominal wall to replace the laparoscopic surgical space built by CO_2_, with the aim of avoiding pneumoperitoneum-related complications and improving the safety of laparoscopic surgery.

Although studies have shown that minimally invasive radical hysterectomy has a worse survival rate, some surgeons may consider continuing to use this method because it may reduce the rate of surgical complications/mortality of surgery.

Therefore, based on the above research background, our surgical purpose is to reduce the possibility of tumor proliferation and tumor cell dissemination while retaining minimally invasive: (1) gasless laparoscopy surgery and abdominal wall suspension; (2) insert the port into the umbilical foramen to achieve abdominal pressure in the open state, and the smoke from the electrosurgical instrument can be smoothly discharged; (3) without the use of uterine manipulators, close the vaginal resection area before vaginal incision. The laparoscopic cervical cancer surgery in the open state is compared with the traditional open cervical cancer surgery, we hope that patients can still have a good tumor outcome and survival outcome, and a lower recurrence rate while undergoing minimally invasive procedures. Recurrence rates and characteristics, complications and incidence rate, impact on quality of life, and cost-effectiveness will also be determined.

## Patients and methods

### Design

This trial is designed as an open-label, randomized phase III trial. The study protocol was approved and registered by the Ethics Committee of Shenyang Women’s and Children’s Hospital. The purpose of randomization is to eliminate selection bias. The SPIRIT reporting guidelines were used to ensure the completion of the study protocol (Additional file 1) [17]. The study flowchart is illustrated in Fig. 1.

**Fig. 1 Fig1:**
[figure not shown]
Trial design

### Patients

Patients who meet the eligibility criteria below will be recruited from our clinic. Oral and written information about the study will be provided by the examining doctor.

### Inclusion criteria

Age ≥ 18 yearsAdenocarcinoma, squamous cell carcinoma, or adenosquamous carcinoma of the cervixECOG performance status of 0–1FIGO (2018) clinical stage IA1 disease with lymphovascular space invasion, IA2 disease, or IB1 disease (< 2 cm and limited to the cervix)Patients could undergo either a type II or a type III radical hysterectomy (Piver classification) and pelvic lymphadenectomyPostoperative adjuvant radiation therapy was recommended according to the Sedlis criteria, which are widely accepted [18]

### Exclusion criteria

Neuroendocrine, clear cell, or serous cell typeClinically advanced disease (stages IB2–IV) with a tumor size larger than 4 cmUterine size larger than 12 cm in lengthA history of abdominal or pelvic radiotherapyEvidence of metastatic disease on positron-emission tomography–computed tomography, magnetic resonance imaging, or computed tomographyTo be unable to undergo surgery or unable to withstand lithotomy and steep Trendelenburg positionLack of compliance or living too far from a treatment center, thus not allowing adequate follow-up

### Study assessments and procedures

The study assessments and procedures were performed at baseline and 1 week, 6 weeks, 3 months, and follow-up visits begin at 3 months following surgery and continue every 3 months thereafter for the first 2 years and every 6 months until year 4.5 (Table 1) [8].

**Table 1 Tab1:** Schedule of patient assessments

	Baseline (within 30 days of day 1)	Surgery	1 week	6 weeks	3 months (± 14 days)	6 months (± 14 days)	Follow-up^a^

### Who will take informed consent?

Researchers at participating institutions should adequately inform study participants about the trial in advance. After giving potential participants enough time to consider whether or not to participate, The investigators obtained their written informed consent.

### Additional consent provisions for the collection and use of participant data and biological specimens

We will request consent for review of participants’ medical records, and for the collection of cervical tissue to assess for cancerous cells.

## Interventions

All surgeries will be performed by the same experienced surgeon. The surgeon is a chief physician with 30 years of clinical experience, proficient in minimally invasive and open surgery techniques for early cervical cancer.

### Abdominal radical hysterectomy

Antibiotics were given 30 min before surgery; a sequential compression device (SCD) was used. Make a median incision in the abdomen, all peritoneal surfaces should be thoroughly examined, the location of any metastatic disease should be recorded in the surgical report, and a biopsy should be performed to confirm the diagnosis. The posterior pelvic peritoneum was opened, suspected enlarged lymph nodes were removed, and frozen sections were submitted for examination. If the lymph nodes are positive, the aortic lymph nodes are sampled, but radical hysterectomy will be abandoned and the patient will receive definitive chemoradiotherapy. If the pelvic lymph nodes are not suspected, radical hysterectomy (Piver type 2 or 3) and pelvic lymph node dissection are possible, and the ovaries may be removed or preserved and/or transposed. Staging of aortic lymph node dissection includes removal of lymphoid tissue to submesenteric artery tissue. The days of catheter indwelling were recorded after operation.

### The laparoscopic cervical cancer surgery in the open state

Antibiotics were given 30 min before surgery; a sequential compression device (SCD) was used.To establish laparoscope operation in an open state: ① Cut a 2-cm incision in the navel and place a single port. Open the abdominal cavity, which is connected to the outside world, and the intra-abdominal pressure is consistent with the state of the open surgery. ② A 10-mm incision was made 5 cm above the umbilicus, a 10-mm trocar was punctured into the abdominal cavity, and a laparoscope was inserted. ③ A 1.0–1.2-mm steel needle was inserted subcutaneously along the white line from 4 cm above the pubic symphysis to 2 cm below the umbilicus. The suspension rod was fixed on the right side of the patient's waist, and the lifting rod crossed the white line of the abdomen. A chain with a steel needle gripper was hung on the cross bar of the suspension rod, and the suspension height of the abdominal wall was adjusted through the chain.④The auxiliary operation hole was the same as the normal laparoscopy operation hole, and the number of ports used to perform the procedure is up to the surgeon’s discretion.No manipulator, close the vaginectomy before incision. Specific operations are as follows:

Transvaginal sealing of cervical cancer ensures that the whole laparoscopic radical hysterectomy(LRH)operation is completed without tumor exposure. After satisfactory anesthesia, the patient took the bladder lithotomy position, performed routine disinfection, sewed the anal protective towel in the perineal water to prevent pollution, and fixed the bilateral labia minora. After vaginal disinfection again, the upper and lower vaginal hooks exposed the vagina and cancerous cervix, and the length of the vagina to be removed was determined according to the scope of lesions (usually ≥ 3 cm). Six tissue forceps were used to clamp the four walls of the vagina at the lower edge of the vaginal wall to be removed, Inject a water pad (1 mg adrenaline diluted with 500 mL normal saline) under the mucosa of the intended vaginal excision with a syringe to facilitate the separation of the vaginal wall from the bladder and rectum and reduce bleeding. Cut the vaginal wall in a circular way along the clamp of the tissue forceps with a unipolar electric knife and slightly mechanically separate it. Suture the nodules on the front and rear walls of the initially separated lower edge of the vagina to seal the cervical cancer. While pulling the suture downward, pull the hook upwards to pull the bladder and rectum, adhere to the vaginal wall along the bladder vaginal gap and rectum vaginal gap, and use sharp scissors combined with blunt fingers to further separate the vaginal wall to be removed until the bladder and rectum are folded peritoneum. At the same time, further expand the separation to both sides, reaching the knees of both ureters in the front and the bilateral uterosacral ligaments in the back. The adjacent vaginal tissues on both sides are cut off by external forceps, Suture the broken end. In order to ensure the principle of tumor free to the greatest extent, rinse the vagina with saline again and collect the washing solution for tumor cytology. After the second iodophor disinfection, the front and back of the vagina are filled with gauze to reach the front and back of the retroflex peritoneum, and then start the laparoscopy. The fundus sutures were pulled instead of lifting the uterus. The absorbable line No. 1 was used to perform Fig. 8 sutures on the fundus. The intraoperative assistant clamps the suture line to swing the uterus to avoid the use of lifting the uterus.

All peritoneal surfaces should be thoroughly examined, the location of any metastatic disease should be recorded in the surgical report, and a biopsy should be performed to confirm the diagnosis. The posterior pelvic peritoneum was opened, suspected enlarged lymph nodes were removed, and frozen sections were submitted for examination. If the lymph nodes are positive, the aortic lymph nodes are sampled, but radical hysterectomy will be abandoned and the patient will receive definitive chemoradiotherapy. If the pelvic lymph nodes are not suspected, radical hysterectomy (Piver type 2 or 3) and pelvic lymph node dissection are possible, and the ovaries may be removed or preserved and/or transposed. Staging of aortic lymph node dissection includes removal of lymphoid tissue to submesenteric artery tissue. Closure technique for the vaginal vault is left to the discretion of the surgeon; Alternatively, the laparoscopic procedure may be completed vaginally.

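### In the gasless arm the vagina is divided and sealed before nodes are assessed, so the rule to abandon surgery for positive nodes falls after part of the resection, while in the open arm it falls before

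*Protocol article*

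**What the plan says.** The protocol article describes the two operations under Interventions.

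**Open arm (Abdominal radical hysterectomy).** After a midline incision the peritoneum is inspected, suspicious nodes are removed for frozen section, and a decision follows. If nodes are positive, "radical hysterectomy will be abandoned and the patient will receive definitive chemoradiotherapy". If nodes are not suspicious, the radical hysterectomy can go ahead.

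**Gasless arm (The laparoscopic cervical cancer surgery in the open state).** The section first describes ports, laparoscope and abdominal wall suspension, and then a transvaginal stage:

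- division of the vagina: "Cut the vaginal wall in a circular way along the clamp of the tissue forceps with a unipolar electric knife"
- closure over the tumour: "Suture the nodules on the front and rear walls of the initially separated lower edge of the vagina to seal the cervical cancer"
- further separation, "reaching the knees of both ureters in the front and the bilateral uterosacral ligaments in the back"
- division of the lateral tissue: "The adjacent vaginal tissues on both sides are cut off by external forceps"
- packing, after which laparoscopy begins: "the front and back of the vagina are filled with gauze to reach the front and back of the retroflex peritoneum, and then start the"

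Peritoneal inspection and frozen section are described only after this. The rule is then the same as in the open arm: "If the lymph nodes are positive, the aortic lymph nodes are sampled, but radical hysterectomy will be abandoned and the patient will receive definitive chemoradiotherapy".

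**The concern.** One decision rule is written for both arms, but the operations reach it in different states. An open-arm patient with positive nodes leaves the operation with uterus and vagina undivided. A gasless-arm patient with the same finding has, on the stated order, already had the vagina divided and closed over the tumour, and tissue beside the bladder, rectum and ureters dissected. That part cannot be undone. The protocol does not say what abandoning the operation means from there.

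Two things are at stake:

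- **Safety.** The added surgical exposure falls only on the gasless arm, in patients for whom the protocol's own rule says the radical operation should not proceed. The protocol treats fistula as a stopping concern (Criteria for discontinuation of trial treatment; Discontinuation of the study).
- **Accounting.** Efficacy is analysed by intention to treat and toxicity by treatment received (Phase II analysis). The article does not say how a gasless-arm patient with an abandoned hysterectomy is classed. Complications of the vaginal step could therefore be counted outside the gasless group, although the 8% complication limit for continuing the trial is set on that group.

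**Working it through.** No formula applies, and the plan gives no figure to reproduce. The check is to set out the step order in each arm and to look for any text that puts nodal assessment before the vaginal work.

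| Step | Open arm | Gasless arm, as written |
|---|---|---|
| 1 | Abdominal incision | Ports, laparoscope, wall suspension |
| 2 | Peritoneal inspection | Circumferential division of the vagina |
| 3 | Suspicious nodes to frozen section | Cuff sutured over the tumour |
| 4 | Abandon or proceed | Dissection to ureteric knees and uterosacral ligaments; lateral vaginal tissue cut and sutured |
| 5 | Radical hysterectomy if proceeding | Packing, then laparoscopy starts |
| 6 | – | Peritoneal inspection |
| 7 | – | Suspicious nodes to frozen section |
| 8 | – | Abandon or proceed |

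The decision stands at step 4 in the open arm, with no vaginal step before it. In the gasless arm it stands at step 8, after the vaginal work of steps 2 to 4.

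Two places might have put nodal assessment earlier in the gasless arm:

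1. **Access set-up.** The laparoscope is inserted before the vaginal text begins. No inspection or nodal step is described there, and the later text explicitly starts the laparoscopy after the vaginal work. This leaves the order less than fully clear, but it does not move the nodal decision forward.
2. **Table 1.** Sentinel lymph node biopsy is ticked under surgery, with no timing relative to the vaginal step.

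**Number of patients.** The documents give no rate of positive nodes at operation. Purely for scale, assume 1% to 10% of the 370 patients in the gasless arm:

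- 370 × 0.01 = 3.7, about 4 patients
- 370 × 0.10 = 37 patients

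The eligibility rules favour the low end. Tumours are IA1 with lymphovascular invasion, IA2, or IB1 below 2 cm; metastatic disease on imaging is excluded; and frozen section is described only for nodes that look suspicious.

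**The case against.** The strongest reply has four parts.

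- **The instructions do not exclude each other.** A reader might infer that the gasless-arm text cannot be followed as written. That goes too far. After the vaginal stage the uterus is still in place, so the surgeon can stop and refer the patient for chemoradiotherapy. What stands is that the same rule is applied in a different state, which the text does not define.
- **Early sealing is part of the technique.** The Introduction lists closure before the vaginal incision among the features of the new operation, and the operative text gives avoidance of tumour exposure as the reason. A reader might infer that the step order is a nuisance separate from the technique under test and that it biases the intention-to-treat comparison. The documents do not support this: an effect of early sealing belongs to the assigned strategy, and intention to treat captures it. But the stated reason does not address the patient whose nodes prove positive.
- **The real sequence may differ.** The laparoscope is in place before the vaginal text starts, so an early look is not ruled out. This is fair, and it limits certainty about practice. It is also a reason to state the order plainly.
- **An article condenses the protocol.** True, but here the sequence is printed in detail. The point rests on what that sequence says, not on something left out for brevity.

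**Conclusion.** The point holds in limited form. On the printed order, a single abandonment rule is applied before any vaginal or uterine resection in the open arm and after an irreversible part of the resection in the gasless arm. The meaning of abandonment in the second case is undefined. This is mainly a matter of patient safety and of unequal application of one rule.

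Its size is unknown. The 4 to 37 patients above rest on an assumed rate and show scale only. A reader might go on to infer a shift in 4.5-year disease-free survival and set it against the non-inferiority margin. The documents give neither a node-positive rate nor any outcome after vaginal division and chemoradiotherapy, so no such shift can be derived.

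The conclusion assumes that the operation follows the order of the text. If nodes are in fact assessed before the vagina is divided, the inequality disappears and the text needs correcting.

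**What to change.** - The sponsor's clinicians should reconcile the two operative sections on one question: when are peritoneum and nodes assessed relative to the transvaginal step in the gasless arm? The order is theirs to choose; none is proposed here.
- They should also state what abandonment means, and how care continues, if the transvaginal step is already complete.
- Record every abandoned radical hysterectomy by arm, with the operative step reached, in one case report form field.
- Keep these patients in the intention-to-treat set. Count any complication of the vaginal step in the gasless arm's safety data, whatever operation was completed.
- Report the counts by arm to the data monitoring committee. The planned safety look after 100 patients is a natural first occasion.

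The cost is a short amendment and one data field. If the order of steps changes, some operating time may be added in the gasless arm. No extra patients are needed.
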